## Abstract

Detrimental health consequences of smoking for both parents and children stress the importance for parents to quit. A Dutch efficacy trial supported the efficacy of proactive telephone counseling on parents. Still, how this program would function in “real world” conditions and how parents could be optimally reached is unclear. Therefore, this study will use an innovative method to examine the recruitment success of two implementation approaches (i.e., via a healthcare approach and a mass media approach) to test the (cost)effectiveness of the program. A two-arm randomized controlled trial and an implementation study (i.e., process evaluation) are conducted. Parents (*N* = 158) will be randomly assigned to the intervention (i.e., telephone counseling) or control conditions (i.e., self-help brochure). Primary outcome measure is 7-day point prevalence abstinence at three months post-intervention. Qualitative and quantitative research methods are used for the process evaluation. We expect that parents in the intervention condition have higher cessation rates than parents in the control condition. We also expect that the recruitment of parents via (youth) health care services is a more promising implementation approach compared to mass media. Results will have implications for the effectiveness of a proactive telephone counseling and provide directions for its successful implementation.

## 1. Introduction

Cigarette smoking continues to be the most preventable cause of mortality and morbidity [1]. In the Dutch population of 17 million people, close to 19,200 people died from smoking-related diseases (e.g., lung cancer and Chronic Obstructive Pulmonary Disease (COPD)) in 2014 [2]. In addition, in 19% of Dutch families with children younger than 18 years, children are exposed to indoor smoking [3]. Exposure to Environmental Tobacco Smoke (ETS) has detrimental effects on children’s physical health, including increased incidences of middle ear disease, reduced lung function, and increased frequencies of childhood asthma and bronchitis [4,5]. It is important that parents quit smoking to eliminate the majority of the children’s ETS [6] and diminish the risk for children to start smoking [7,8]. Moreover, it reduces the odds of morbidity and mortality for smoking parents themselves [9].

The existing research suggests that most parents want to quit smoking and even tried to quit smoking [10]. In addition, most parents would accept smoking cessation support, such as telephone counseling [11]. A review consisting of 77 (quasi) randomized controlled trials (RCT) on telephone counseling confirmed that telephone counseling is effective in increasing smoking cessation rates [12]. Moreover, Hollis et al., 2007 [13] found that telephone counseling is cost-effective (i.e., the degree to which something is effective in relation to its costs). Recently, a tailored telephone counseling program for smoking parents was tested in The Netherlands [14]. Parents who smoke (*N* = 512) were recruited in an RCT and assigned to the intervention condition (i.e., tailored telephone counseling and supplementary materials) or the control condition (i.e., a standard self-help brochure). Parents who received telephone counseling were more likely to report 7-day point prevalence abstinence at three months post-intervention (44.5% versus 12.1%; OR = 6.89, 95% CI = 4.18–11.36) and to use nicotine replacement therapy (48.4% versus 20.9%) compared to parents who received a standard self-help brochure. Among parents who did not quit smoking, those who received telephone counseling were more likely to make a quit attempt (85.2% versus 68.1%) and to implement a complete home smoking ban (39.5% versus 26.1%) compared to parents who received the self-help brochure. Altogether, this study provided evidence that telephone counseling tailored to smoking parents is effective in helping parents quit smoking and developing parenting practices that protect their offspring from ETS exposure [14].

Although Schuck et al., 2014 [14] found that the telephone counseling was effective, they tested it in an efficacy trial. This means that the telephone counseling was evaluated under optimum conditions [15]; the counseling was offered for free, and participating parents were rewarded with 100 euros after completing the study. Therefore, how the telephone counseling would function when examined in “real world” conditions (i.e., in an effectiveness trial) is unclear. Moreover, despite its effectiveness, intervention success also depends on the extent to which people have access to the program and the acceptance and utilization of these programs [16]. An important predictor of the reachability of smoking cessation programs concerns their recruitment strategy [17]. Recruitment strategies can be classified into proactive recruitment strategies (i.e., people are contacted directly, and services are offered to them) and reactive recruitment strategies (i.e., people are informed about the availability of an intervention and those who are interested have to volunteer to participate) [18]. Many programs use a reactive recruitment strategy [19], which could explain why only a minority of smokers use smoking cessation programs [20]. In contrast, proactive recruitment strategies have proven to be effective in improving the reachability of smoking cessation programs [16,21,22] and in promoting smoking cessation among smokers [23,24,25].

In addition to recruitment strategies, recruitment venues are also important aspects of the reachability of smoking cessation programs. In the Dutch efficacy study, primary schools were used to recruit smoking parents for a telephone counseling [22]. According to the authors, primary schools can reach the majority of smoking parents and function as a ‘teachable setting’ for smoking parents [22]. The results of this study have shown that the primary schools are willing to promote telephone smoking cessation counseling to parents. In addition, this recruitment channel resulted in relatively low recruitment costs (21.74 euros per parent) and a high reach (approximately 10,000 households). However, despite the low costs, the response rate was low (5%), even though participating parents were rewarded with 100 euros after completing the study. The effect of the financial reward of 100 euros for the participants’ willingness to participate on the response rate of smoking parents of children in primary schools is unclear. Further research is needed to gain insight into whether primary schools are a good implementation channel to connect smoking parents with a proactive telephone smoking cessation counseling.

Online mass media (e.g., smoking cessation websites and social media) is another promising channel that could connect parents who smoke with a proactive telephone counseling. In The Netherlands, smokers who are interested in smoking cessation can visit various smoking cessation websites, including the national online smoking cessation website (i.e., www.ikstopnu.nl). This website, funded by the Dutch government, had 89,116 unique visitors in 2016 [26]. Some studies have provided evidence that online mass media can be successful and cost-effective in recruiting smokers for cessation support [27,28,29]. However, to our knowledge, little is known about whether online mass media is successful in connecting parents who smoke to a proactive telephone counseling. Hence, further research is needed to assess the implementation of this program.

In addition to a mass media approach, the health care setting can also be suitable for addressing parental smoking [30,31,32]. Winickoff and colleagues (2001) [33] found that 74% of smoking parents whose children are hospitalized would enroll in a free telephone counseling cessation program. Moreover, these parents are also more motivated to quit smoking, since they worry more about the consequences of their smoking for their children’s respiratory diseases [34]. In The Netherlands, youth health care could be an ideal setting to address parental smoking cessation, as the Dutch youth health care provides preventive health care to all children (aged 0 to 17 years old) [35]. In The Netherlands, all parents must visit youth health care centers 15 times in the first four years of their child’s life [35]. In addition, youth health care professionals are expected to address parental smoking (cessation) at least four times during that time, if applicable [36]. Research shows that it is considered to be the (youth) health care professional’s role to address parental smoking [37,38,39]. However, (youth) health care professionals experience several barriers in doing so (e.g., a lack of time, the possibility of damaging the doctor-patient relationship, and lack of confidence in own smoking cessation counseling skills) [38,39,40]. Therefore, it is essential to provide a convenient, user-friendly, and time-saving intervention to (youth) health care professionals that does not jeopardize the doctor-patient relationship. In the present study, a time-saving and convenient intervention will be provided that allows (youth) health care professionals to easily refer smoking parents to a telephone counseling (see the methods section for an elaborate description of our intervention).

In sum, this effectiveness study takes a novel method by examining the recruitment success of two implementation approaches (i.e., a mass media approach and a health care approach) to test the (cost)effectiveness of a telephone smoking cessation counseling and whether the effectiveness depends on the implementation approach. The mass media approach includes two implementation channels: mass mailings through primary schools and online mass media. The health care approach also consists of two implementation channels: general health care and youth health care. A 2-arm RCT will be carried out to test the (cost)effectiveness of the telephone counseling. Based on earlier results of Schuck et al., 2014 [14], it is expected that parents who receive telephone counseling show higher smoking cessation rates at 3-month post-intervention compared to parents who receive the control condition. Concerning the implementation of the telephone counseling, a process evaluation of the recruitment success will be conducted for two implementation approaches. It is expected that (youth) health care will be a more promising implementation approach for connecting smoking parents with the telephone counseling compared to mass media channels (online approach and mass mailings trough primary schools), as most of these parents are motivated to quit and find it acceptable to be directed to telephone counseling in the context of their child’s health [11,34].

## 2. Materials and Methods

### 2.1. Study Design

Because both the (cost)effectiveness and the implementation strategy of the telephone counseling will be examined, an effectiveness-implementation hybrid design will be adopted. This design has multiple advantages, including improving the capability to identify important implementation strategies and interactions, increasing the speed of implementing the interventions once deemed effective, and providing valuable information for decision makers [41,42]. With respect to the RCT, parents who smoke will receive two online questionnaires during a period of three months. In total, 158 smoking parents will be randomly assigned to the intervention (i.e., telephone counseling) or control (i.e., self-help brochure) condition. The study design is depicted in Figure 1.

### 2.2. Participants and Recruitment

In total, 158 smoking parents will be recruited through four different implementation channels (i.e., primary schools, online mass media, health care, and youth health care), which will be distinguished as two different implementation approaches (mass media approach and health care approach).

#### 2.2.1. Mass Media Approach

##### Primary Schools

A random sampling strategy will be used to recruit smoking parents through their children’s primary schools across all 12 provinces of The Netherlands. The randomly selected primary school boards will be asked to (1) distribute invitation letters to all children (aged 4–12 years) and ask children to hand these letters to their parents or (2) send the letters directly to the parents via e-mail. The primary schools decide which option they prefer. The invitation letters, which are targeted on parents in general and not personalized, will include a description of the study’s purpose, frequency of the assessments, and inclusion criteria. Smoking parents recruited via primary schools will be able to register for the study by completing the registration form (active informed consent) on the study website or by returning the form via mail. After the completion of the registration form, the parents will be called by professional counselors of SineFuma (one of the Dutch certified quit lines). During this phone call conversation, parents will receive additional information about the study (e.g., parents who will be randomized to the telephone counseling might have to pay for the telephone counseling (based on the parents’ health insurance), whereas parents who are randomized to the control condition do not have to pay for their intervention) based on which they will either confirm or withdraw their registration.

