##### Online Mass Media

Parents will be recruited through social media and two smoking cessation websites, including the Dutch national smoking cessation website. With respect to social media, multiple paid Facebook advertisements will be created and used for several months. The advertisements will target on parents who are interested in smoking (cessation). Both format and message of the advertisements can differ, depending on what message and/or format will be more successful in recruiting parents who smoke. Whether advertisements are successful or not will be based on the click through ratio (i.e., the ratio of users who click on the Facebook ad of the total users who view the ad) and the costs per click on the ads. Parents who will be recruited through online mass media have to complete a short registration form (i.e., name, telephone number, and e-mail address) on the website of SineFuma so that they can be called by the coaches within one week. Parents who will fulfill the inclusion criteria will be given a description of the study. Parents who will not fulfill the inclusion criteria will not be included in the study, but they will be offered telephone counseling. Parents who will be willing to participate in this study will receive a registration form and will be asked to return the completed form (active informed consent) by mail or online on the study website.

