#### 2.2.2. Health Care Approach

General health care and youth health care professionals (henceforth referred to as health care professionals) will be recruited using multiple methods, e.g., word of mouth among health care professionals and social media (i.e., Facebook and LinkedIn). Participating health care professionals will receive materials to be used for support. When smoking parents come to see a health care professional, they will be asked whether they want to receive effective smoking cessation support and whether they want a smoking cessation coach to call them. When parents give their permission, health care professionals will be able to register them online by telephone or by fax. Subsequently, professional counselors of SineFuma will contact these parents within one week. The registration process for the study will be identical to the registration process through online mass media.

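### Order of offer is confounded with channel: school parents consent to a study before any call, while parents in the other three channels agree to a coach's call first

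*Protocol article*

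**What the plan says.** **Schools (Section 2.2.1, Primary Schools).** The invitation letter "will include a description of the study’s purpose, frequency of the assessments, and inclusion criteria". Interested parents "will be able to register for the study by completing the registration form (active informed consent) on the study website", or return the form by post. The call follows: "After the completion of the registration form, the parents will be called by professional counselors of SineFuma". In that call parents hear more about the study, including possible costs, and confirm or withdraw.

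**Online (Section 2.2.1, Online Mass Media).** The parent's first act is a short contact form "on the website of SineFuma so that they can be called by the coaches within one week". The study comes next: "Parents who will fulfill the inclusion criteria will be given a description of the study". Consent is given on a registration form after that.

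**General and youth health care (Section 2.2.2).** When parents see a professional, "they will be asked whether they want to receive effective smoking cessation support and whether they want a smoking cessation coach to call them". After that, "The registration process for the study will be identical to the registration process through online mass media".

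**Use of the results.** The Introduction groups schools with online as the mass media approach and predicts that health care will be the more promising approach. It also says research is needed on "whether primary schools are a good implementation channel to connect smoking parents with a proactive telephone smoking cessation counseling". Section 2.11 defines recruitment success, per channel and per approach, as sign-ups for a coach's call divided by parents who start the intervention. Section 4 would drop a channel whose recruitment is extremely low and/or whose quit rates are low. The limitations in Section 3 do not mention the different entry routes.

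**The concern.** One of the four channels enrolls study-first and three enroll call-first. A parent who wants counseling but not research can sign up in three channels and cannot sign up in the fourth. The Introduction asks whether schools can connect parents with counseling, and a research invitation does not answer that cleanly.

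The imbalance carries into the main implementation comparison. Health care is wholly call-first, whereas mass media mixes study-first schools with call-first online. A difference between approaches in recruitment could come from the approach, from the order of offer, or from both. The same holds for a difference in cessation effect, because parents who answer a study letter may differ from parents who ask for help.

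The recruitment measure has a further problem. Schools have no separate sign-up for a call, so their only sign-up is the study consent form. Section 2.11 therefore counts schools at a later step than the other channels.

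**Working it through.** **1. The steps side by side**

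| Step | Schools | Online, general and youth health care |
|---|---|---|
| First act by the parent | Study registration with consent | Agrees to a coach's call |
| Second | Counselor's call, confirm or withdraw | Call; study described to eligible parents |
| Third | Start | Study registration with consent |
| Fourth | – | Start |
| Sign-up count in Section 2.11 falls | After study consent | Before study consent |

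**2. What this does to the recruitment ratio**

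The documents give no rates, so this is an illustration on assumed ones. Let I = 200 interested parents in each channel, a = share who accept the study (0.3 to 0.7), and c = share of those who go on to start (0.6 to 0.9).

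- Schools: sign-ups = I·a, starters = I·a·c, ratio = 1/c.
- Call-first: sign-ups = I, starters = I·a·c, ratio = 1/(a·c).

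At a = 0.5 and c = 0.8:

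- Schools: 100 sign-ups, 80 starters, ratio 1.25.
- Call-first: 200 sign-ups, 80 starters, ratio 2.50.

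Over the whole range:

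- Schools: 60 to 140 sign-ups, ratio 1.11 to 1.67.
- Call-first: 200 sign-ups, ratio 1.59 to 5.56.
- Starters: 36 to 126, equal in both routes at any given a and c.

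If only parents starting counseling count as starters, 1:1 allocation doubles both ratios and the contrast stays.

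**3. Direction**

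In step 2 the channels are truly equal, yet three readings disagree. Schools look weaker on sign-ups, better on the ratio (fewer sign-ups per starter), and equal on starters.

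The school ratio does not contain a, so it cannot show parents lost to the research letter. Keep c = 0.8, and suppose 30% accept the study by letter but 70% accept it from a coach. Schools then yield 200 × 0.3 × 0.8 = 48 starters at a ratio of 1.25. Call-first yields 200 × 0.7 × 0.8 = 112 starters at 1/(0.7 × 0.8) = 1.79. The channel with fewer than half the starters has the more favorable ratio.

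**4. Precision of a contrast within one entry route**

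Section 2.7 gives 36 per arm per approach at 44.5% versus 12.1%. A two-sided 5% test with 80% power and continuity correction reproduces 36. Then 2 × 72 = 144, and 144 × 1.10 = 158.4, in line with the stated 158.

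Variance of one log odds ratio at 36 per arm: 1/(36 × 0.445 × 0.555) + 1/(36 × 0.121 × 0.879) = 0.112 + 0.261 = 0.374.

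- Health care versus pooled mass media: √(2 × 0.374) = 0.864. The 95% interval for the ratio of odds ratios runs a factor exp(1.96 × 0.864) ≈ 5.4 either way.
- Health care versus online only, assuming online supplies half of mass media (18 per arm): √(0.374 + 2 × 0.374) = 1.059, a factor of about 8.

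The narrower contrast is free of the order-of-offer difference but imprecise.

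**The case against.** The strongest reply is that an effectiveness-implementation hybrid compares channels as delivered packages. A mailing, an advertisement and a face-to-face referral differ in much besides the form, so one common form would not isolate the channel. Section 2.11 also collects barriers, facilitators, reach and context, which could help explain low school uptake. This stands in part: harmonizing the form removes one difference, not all. But the order of offer is not inherent to schools, since a letter can offer a call and routine delivery would have no study to join. Qualitative data also do not put the count back at a common step.

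Three stronger readings are tempting and not supported.

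- **That the comparisons measure the offer instead of the channel.** They measure both together and cannot separate them.
- **That schools or mass media will be understated.** On the plan's own ratio the bias may favor schools. Section 2.2.1 lists what the letter will include, which does not show that counseling goes unmentioned. The advertisement wording is left open, so it is not shown that online parents know nothing of the study before the call.
- **That call-first controls, having asked for a coach, will quit less out of disappointment and so distort the effect comparison between approaches.** Every randomized parent consented to the study, and Section 2.4.2 offers controls the counseling after the second assessment. The documents give no rates for such an effect. Its direction is open too, because parents who ask for help could be more motivated.

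**Conclusion.** The point holds in a limited form. Order of offer is confounded with channel in every comparison that includes schools and, through pooling, in mass media versus health care. The Section 2.11 sign-up count is not taken at the same step in schools as elsewhere, so the school and mass media recruitment figures are not comparable with the others as planned. The size depends on how many parents who want counseling would also accept a study, which the documents do not give. Under the assumed rates, equal channels show ratios of 1.11 to 1.67 against 1.59 to 5.56. The direction of bias in practice is not known.

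Comparisons among online, general health care and youth health care share one study registration process and are not affected by this difference. The overall counseling versus brochure comparison is protected, because Section 2.6 stratifies randomization by channel.

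**What to change.** **Section 2.2.1, Primary Schools.** Let the letter lead to the same short form requesting a coach's call, with study description and consent following as in Section 2.2.2. The cost is new letter text and more calls that do not end in enrollment. Recruitment is planned from September 2016 to September 2018, so a change partway leaves two school routes, which should be reported apart.

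**For school parents enrolled by the existing letter:**

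- In Section 2.11, count recruitment at the same steps in all four channels: consented to the study, confirmed, started. A confirmation step is described only for schools, so it would need recording elsewhere.
- In Section 2.10, report health care versus online beside the pooled approach comparison. Channel is already a stratification factor, so no new data are needed. Label it supportive and low-precision, and do not use it as a pass-or-fail test of the pooled result.
- In Sections 3 and 4, name the different entry route as a limitation and confine conclusions about schools to the channel plus the offer as delivered.
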